### Statistical analysis

The intervention effects of primary and secondary outcome measures will be analyzed according to the intention-to-treat principle. In addition, a secondary per protocol analysis will be performed in patients with adequate compliance. After initial univariate analyses of differences in the primary outcome between the intervention and control group, multivariate analyses will be used to adjust for potential confounders such as age, gender, baseline values of nutritional status, physical disability, co-morbidity, and mental state including depression.

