## Methods

### Study design, general outline and randomization

Figure 1 shows the design of the study, which is an open-label, randomized controlled, multi-centre trial. Patient allocation to intervention or control group is performed after stratification for hospital, gender, and age (55-74 years vs. 75 years and above). Patients allocated to the intervention group receive dietetic counselling and oral nutritional supplementation for 3 months following surgery. The control group receives usual nutritional care. Patients are enrolled within 5 days after surgical treatment of hip fracture, and baseline measurements are performed immediately after enrolment. Outcome measurements are performed at the patient's home at three and six months following hip fracture. The study has been approved by the Medical Ethical Committee of Maastricht University Medical Centre and Maastricht University and is conducted according to the Declaration of Helsinki.

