### Study population and recruitment of the study population

For patient recruitment, a daily inventory is made of hip fracture patients admitted to the surgical and orthopaedic wards of three hospitals in South-Limburg in The Netherlands: Maastricht University Medical Centre, Maastricht (MUMC); Atrium Medical Centre, Heerlen (AMC); and Orbis Medical Centre, Sittard (OMC). Based on this inventory, eligible candidates are invited to participate and written informed consent is obtained within 5 days after surgery. Inclusion criteria are aged 55 years and above and hospital admission for surgical treatment of hip fracture. Patients are excluded if they have a pathological or periprosthetic fracture; disease of the bone metabolism (e.g. M Paget, M Kahler, hyperparathyroidism); life expectancy of less than 1 year due to underlying disease (e.g. cancer); use oral nutritional supplements before hospital admission; are unable to speak Dutch; live outside the region of South-Limburg, or are bedridden before the hip fracture. Patients who suffer from dementia or who are cognitively impaired according to the Abbreviated Mental Test (AMT) (a score of less than 7) are also excluded [20,21].

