### Outcome assessment

The primary outcome measure is total length of stay in hospital and rehabilitation clinics including hospital readmissions. Secondary outcome measures, assessed at three and six months after hip fracture, are nutritional status, functional status, quality of life, complication rate and one-year mortality.

Assessment of nutritional status includes total food and supplement intake, measurement of body composition, muscle strength and biochemical parameters in blood. Anthropometric measurements are body weight, height, thickness of biceps, triceps, sub scapula and supra-iliac skin fold, and circumference of mid-arm, waist and hip. Body composition is measured by bio-electrical impedance spectroscopy. Biochemical parameters include albumin, pre-albumin, CRP, haemoglobin and hematocrit in blood.

Functional status is measured by the Groningen Activity Restriction Scale (GARS) [22], which assesses disability with regard to (instrumental) activities of daily living, and by the Harris Hip Score to evaluate changes in hip function.

Quality of life is measured using the EuroQoL [23,24] and the Medical Outcomes Study 36-item Short-Form Health Survey [25,26]. Mental state and depression is assessed by the Mini-Mental State Examination (MMSE) and the Hospital Anxiety and Depression Scale (HADS) [27,28]. To measure fatigue, the Checklist Individual Strength (CIS) [29] is used.

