### Sample size/power calculation

Nutritional intervention in hip fracture patients can result in an estimated reduction in total length of hospital and rehabilitation stay by 31.3% (SD: 59.0%). A sample of 75 patients per treatment arm is sufficient to detect this effect with a power of 90% and a two tailed alpha of 0.05. To detect a between-group difference in weight of 2.13 kg (SD: 3.72 kg), a number of 61 patients per treatment arm is sufficient using the same power and alpha.

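### Allocation is stratified by hospital, gender and age band, but the initial primary comparison uses none of them and hospital is not named for adjustment, so the test can be mildly conservative

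*Protocol article*

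**What the plan says.** All references are to the protocol article.

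- **Study design, general outline and randomization:** "Patient allocation to intervention or control group is performed after stratification for hospital, gender, and age (55-74 years vs. 75 years and above". With the three hospitals given under the recruitment heading, this makes 3 × 2 × 2 = 12 strata.
- **Outcome assessment:** "The primary outcome measure is total length of stay in hospital and rehabilitation clinics including hospital readmissions".
- **Statistical analysis:** the sequence opens with "After initial univariate analyses of differences in the primary outcome between the intervention and control group", and no stratification factor is mentioned at that step. Next, "multivariate analyses will be used to adjust for potential confounders such as age, gender, baseline values of nutritional status, physical disability, co-morbidity", the list ending with mental state including depression.
- **Sample size/power calculation:** the primary outcome is planned on an "estimated reduction in total length of hospital and rehabilitation stay by 31.3% (SD: 59.0"%), and "A sample of 75 patients per treatment arm is sufficient to detect this effect" at 90% power and two-sided alpha 0.05.

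Two of the three stratifiers, age and gender, are therefore named for the adjusted analysis. Hospital is not, and the words *such as* leave the list open. The article does not link the analysis to the stratification, does not say how allocation is balanced within strata, and does not say which of the two analyses is decisive.

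**The concern.** Stratified allocation forces the arms to be alike on the stratifying factors. If those factors also predict the outcome, the treatment difference varies less from one randomisation to another than under simple randomisation. A model that omits the factors does not see this: it leaves the between-stratum variance in the residual and reports a standard error that is too large. The interval is then too wide, the test rejects less often than its nominal 5% under the null, and some of the precision bought by stratifying is lost.

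The univariate comparison is exposed to this for all three factors. The adjusted analysis is exposed for hospital only, if hospital stays out. The covariates enter as potential confounders, and that rationale gives no reason to add a factor that the design already balances. The plan could therefore be followed faithfully with hospital in no model. At stake is precision on the primary outcome, not false-positive control.

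**Working it through.** **Inputs from the article.** Difference 31.3%, SD 59.0%, 75 per arm, power 90%, two-sided alpha 0.05 (Sample size/power calculation); 12 strata (randomization and recruitment sections).

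**Assumptions, not in the article.** R², the share of outcome variance explained by the stratifiers, is taken as 0%, 5%, 10% and 20%. Allocation is balanced within strata. The comparison is a normal-theory one of means with total SD held at 59.0%.

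**Step 1: reproduce the stated sample size.** n = 2(1.960 + 1.282)²(59.0/31.3)² = 74.7, so 75 per arm, as stated. The noncentrality at 75 per arm is nc = (31.3/59.0)√(75/2) = 3.249, and the power is Φ(3.249 − 1.960) = 90.1%.

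**Step 2: effect of omitting balanced prognostic strata.** The true standard error is √(1 − R²) times the one the unadjusted model reports. Hence:

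- excess in the standard error = 1/√(1 − R²) − 1
- real type I error = 2[1 − Φ(1.960/√(1 − R²))]
- unadjusted power = Φ((nc − 1.960)/√(1 − R²))
- adjusted power = Φ(nc/√(1 − R²) − 1.960)

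For R² = 10%, √0.90 = 0.949. The excess is 1/0.949 − 1 = 5.4%, the type I error is 2[1 − Φ(2.066)] = 3.9%, unadjusted power is Φ(1.358) = 91.3%, and adjusted power is Φ(1.465) = 92.8%.

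| R² | SE too large by | Real type I error | Power, unadjusted | Power, adjusted | Shortfall (points) | n per arm for 90% if adjusted |
|---|---|---|---|---|---|---|
| 0% | 0% | 5.0% | 90.1% | 90.1% | 0 | 75 |
| 5% | 2.6% | 4.4% | 90.7% | 91.5% | 0.8 | 71 |
| 10% | 5.4% | 3.9% | 91.3% | 92.8% | 1.6 | 68 |
| 20% | 11.8% | 2.8% | 92.5% | 95.3% | 2.8 | 60 |

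Shortfalls are taken before rounding (at 10%: 0.92846 − 0.91284 = 0.0156).

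**Step 3: the model with age and gender.** Only hospital's share of R² matters here. This was simulated under the null with 150 patients, 12 strata, blocks of 4 within strata, three equal hospitals, all of R² placed on hospital, and 6,000 runs per setting.

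| R² (hospital) | Type I, unadjusted | Type I, age and gender | Type I, hospital added | 95% half-width, age and gender | 95% half-width, hospital added |
|---|---|---|---|---|---|
| 0% | 0.047 | 0.048 | 0.049 | 19.04 | 19.05 |
| 5% | 0.045 | 0.045 | 0.050 | 19.01 | 18.54 |
| 10% | 0.039 | 0.038 | 0.050 | 19.04 | 18.06 |
| 20% | 0.031 | 0.031 | 0.050 | 19.02 | 17.00 |

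The simulation error of each rate is about √(0.05 × 0.95/6000) = 0.003. When the prognostic factor is hospital, adjusting for age and gender repairs nothing, and adding hospital restores the nominal level. When hospital does not matter, adding it costs almost nothing (19.05 against 19.04).

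**Step 4: is balance needed?** With R² = 20% on hospital but simple, unstratified allocation, the unadjusted type I error was 0.053. The overstated standard error therefore arises only when allocation really is balanced on a prognostic factor.

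**The case against.** The strongest reply is that this is detail a condensed article leaves to the full protocol or analysis plan. The covariate list is open, and the Confounders section names items such as medication use, fracture type and surgical treatment that the Statistical analysis section does not repeat, so the latter list is clearly illustrative. Nothing in the article contradicts a model that includes hospital. This stands in part: a reader might infer that hospital is excluded from the adjusted model, but the text shows only that it is not named. What remains is that the article does fix a sequence that begins with a comparison ignoring every factor randomised on, and it gives a confounder rationale that does not lead to including hospital.

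A reader might also infer that the intervals are certainly too wide, or that hospital is the factor most strongly tied to total stay because discharge practice and rehabilitation capacity differ by site. The documents support neither. They give no between-site variance and no data on discharge practice or bed supply, and they place all three hospitals in one region. The widening is conditional, and it is nil at R² = 0.

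Finally, the effect is small and on the safe side: the unadjusted test keeps at least the planned 90% power throughout the range. This stands in full and limits the weight of the point.

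**Conclusion.** The point holds in a limited form. The initial analysis of the primary outcome uses none of the three stratification factors, and the adjusted analysis does not name hospital. If the stratifiers predict length of stay and allocation is balanced within strata, omitting them makes the test conservative and less precise than the design allows. For R² up to 10% the effect is slight; at 20% the unadjusted interval is about one eighth too wide. These sizes rest on assumed R² values and a normal-theory comparison of means; the article names no test. For the model with age and gender, R² must be read as hospital's share alone.

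It would be wrong to conclude that the trial is underpowered or that its type I error is inflated. The error runs the other way, and the stated sample size reproduces. Confidence is high on what the text says and on the direction of the effect, and low on its size.

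**What to change.** State one primary analysis of total length of stay: a model comparing intervention with control that includes hospital, gender and age together with the baseline covariates already named. Label the univariate comparison supportive. This also settles which of the two results is decisive, and it should be written down before length of stay is compared between arms.

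The cost is wording in the analysis plan. The three factors are known for every randomised patient because allocation used them, so no new data or patients are needed. The main effects take 2 + 1 + 1 = 4 degrees of freedom (hospital, gender, age band) from about 150 patients.

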## Discussion

Patient recruitment has started in July 2007 and has ended in December 2009. Follow-up of the patients is to be completed in June 2010, except for data of one-year mortality. First results are expected in 2011. We expect that this study will answer the question whether nutritional intervention in hip fracture patients improves their nutritional and functional status, resulting in a shorter length of stay in hospital and rehabilitation clinics, fewer postoperative complications, lower mortality, and cost-effectiveness.
